### Treatments

#### Intervention: Group Schema therapy (GST)

GST will consist of 26 weekly 90-minute group sessions, tailored to people with an ED. If necessary, GST can be supplemented with 8 individual sessions used for facilitating the GST process. The individual sessions can for example be used for imagery rescripting of adverse childhood experiences. Subsequent to randomization, patients may have to wait for at most three months before initiating their GST treatment in mental healthcare, as it is a half-open group, with an entry and exit moment every 13 weeks. During this waiting period, 5 individual treatment sessions will take place that focus on explaining the ST model, placing the ED symptoms and behaviors in the context of coping modes, and organizing these in a mode map conceptualization. This is an important foundation for the upcoming GST. The following sessions focus on recognizing and changing personal coping modes regarding eating disorder symptoms and underlying early maladaptive schemas. These sessions are also aimed at developing and strengthening the healthy adult mode. In doing so, GST combines interpersonal, experiential, cognitive and behavioral elements in a unified ST approach. On top of that, a psycho-education webinar will be organized for relatives.

**Theoretical framework for GST: a group format of ST.** In short, ST provides an integrative approach that is fundamentally geared towards treating people with deeply entrenched self-identity difficulties and interpersonal problems, which are reflected through maladaptive schemas and schema modes [15]. In clinical practice, ST was deemed effective for treating personality disorders [16], including ST in a group setting [18]. On the one hand, maladaptive schemas refer to a pervasive pattern of beliefs regarding oneself and one’s relationship with others consisting of one’s memories, emotions, cognitions and bodily sensations. On the other hand, schema modes are characterized by one’s moment-to-moment thoughts, feelings and behaviors when maladaptive schemas interact with coping mechanisms [23].

In terms of treatment delivery, ST emphasizes experiences, while CBT-E mainly emphasizes cognitions and behavior. In GST, the connection between participants in the group format is considered an amplifier for the effects of ST. On top of that, GST ensures a healthy therapeutic relationship to provide corrective experiences in favor of the patient’s needs during treatment [23].

#### Control treatment: individual enhanced cognitive behavioral therapy for eating disorders (CBT-E)

In general, CBT-E is a transdiagnostic ED treatment, meaning that it is widely used for most diagnosed EDs in mental healthcare. In addition to that, it is also considered the current standard of care for most EDs. An entire CBT-E trajectory consists of 20–40 individual sessions, each of which will last 60 min at most. In the current protocol, the first 8 CBT-E sessions for a patient will take place before randomization (phase 1 CBT-E). After being randomized to the continued CBT-E arm, the remaining 12–32 individual sessions will take place.

From a theoretical perspective, CBT-E is based on a so-called transdiagnostic CBT model consisting of four phases. In phase one, patients formulate a personal goal, in which they learn to monitor and establish regular eating behaviors in order to address their eating disorder. In doing so, patients are offered psycho-education on factors that are maintaining their eating disorder. In phase two, consisting of one session, a more specific treatment plan is developed, based on an evaluation of the first phase. During phase three, the identified main mechanisms that are hypothesized to maintain the patient’s ED are addressed. These are (1) an excessive evaluation of body image, (2) dietary restraint, and (3) events, mood and eating. Subsequently, a relapse plan is developed in order to maintain the newly established eating behaviors when faced with these challenging mechanisms. Lastly, phase four aims to evaluate and sustain the total progress that has been achieved during the prior phases.

#### Discontinuation/modification of treatment

In case of acute crisis, the crisis procedures of the treatment centers will be followed. Any additional treatment will be recorded by the therapists and included in the analyses. Patients will only be withdrawn from the study at their request. All (serious) adverse events reported either by the patient, the clinicians, or researchers will be recorded.

### Data collection

Collection of all outcome data will take place on multiple occasions during the trial. Prior to randomization, the EDE-Q will be measured on two different points in time: during the pre-measurement and post-measurement of phase 1 CBT-E. Additional clinical instruments will be used during the pre-measurement of phase 1 CBT-E to measure demographic and clinical characteristics, childhood trauma, perfectionism, and early maladaptive schemas at baseline.

In order to practically operationalize data collection, a digital data handling system will be used. In short, this system is aimed at facilitating informed consent, recruiting and guiding each new research participant automatically to all online measurements in accordance with privacy regulations in Dutch mental healthcare, based on each participant’s individual care trajectory and timeline during the trial. Using an iterative approach with test data to eliminate dysfunctional steps in this automated process, a sophisticated data collection system will be established, presenting all questionnaires in an organized manner with encouraging cartoon pictures. Each measurement will be completed either through hand-based devices (e.g. a smart-phone) or on a computer. From a design perspective, the possibility of using different devices and showing encouraging cartoon visuals may motivate participants to complete online surveys [36]. Data is collected with a pseudonym for each patient. A list of pseudonyms and identifying information of patients is securely stored at the mental healthcare centers and only accessible for the research assistant and coordinator of this center and the authorized researchers. The data is stored on a secure storage server of Maastricht University, accessible only to authorized researchers. The project leaders will be responsible for data monitoring. The study will not be audited. The results of the study will be disseminated in scientific and clinical journals and presentations at (inter)national scientific and clinical conferences.

Subsequent to randomization, participants will complete measures before continued CBT-E or the start of GST (T0), immediately after the confirmed end date of treatment (T1), and 6 months (T2) and 12 months (T3) following completion of treatment. In addition to measuring perceived ED schemas, data on quality of life and healthcare service use will also be gathered on these occasions. Data on process evaluations, as assessed by session rating scales and patient registration files, will be collected during each treatment session of phase 1 CBT-E, continued CBT-E, and GST. After treatment (T1), a representative sample of ED patients from both arms will be recruited to participate in a qualitative interview to gain deeper insights into their treatment experiences. Due to the nature of the interventions, blinding of therapists, interviewers, and patients is not possible. Below, all measures are stratified for clinical effectiveness, economic evaluation and process evaluation.

#### Clinical effectiveness

A distinction is made between primary and secondary outcome data in order to assess clinical effectiveness.

I.Primary outcome.

ED pathology is the primary outcome measure, which will be assessed using the Eating Disorder Examination-Questionnaire [37]. The EDE-Q is a valid and reliable instrument [38], which is sensible to change [39].

II.Secondary outcomes.

Early maladaptive schemas will be measured, using the Young Schema Questionnaire Short Form version 3 (YSQ-S3). It is considered a valid and reliable instrument for the purpose of assessing maladaptive schemas in clinical and research settings [40, 41].

The Schema Mode Inventory for Eating Disorders (SMI-ED) will be applied to identify specific schema modes that are relevant in ED patients. In short, it measures maladaptive child modes, maladaptive internalized modes, maladaptive coping modes and healthy factors, and has adequate validity and high reliability [42].

To rate general psychological and physical symptoms the Brief Symptom Inventory (BSI) will be used, which is highly validated and very sensible to detecting change [43].

Quality of life in ED patients will be assessed using the Eating Disorder Quality of Life (EDQOL) questionnaire. The EDQOL focuses on distinct life domains that are relevantly impacted by eating disorders, and has shown good validity, reliability and sensitivity [44].

Generic quality of life will be measured using the well validated EQ-5D-5 L [45, 46]. This instrument aims to measure quality of life objectively, using five questions regarding quality of life in five distinct domains: mobility, self-care, usual activities, pain / discomfort, and anxiety / depression. Additionally, a 100 mm VAS scale is used to assess a patient’s perceived quality of life [47].

Clinical perfectionism will be assessed using the Clinical Perfectionism Questionnaire (CPQ). In short, this 12-item questionnaire measures the extent to which an individual strives towards extremely high personal standards in the face of adverse consequences. The CPQ is deemed a reliable measure in ED samples [48, 49].

Since childhood trauma may affect ED treatment outcomes, the validated Childhood Trauma Questionnaire-Short Form (CTQ-SF) will be included. It consists of 28 questions measuring physical abuse, emotional abuse, sexual abuse, physical neglect and emotional neglect during childhood [50].

Demographic and clinical characteristics will be identified at baseline, using a tailored list of questions on current treatment expectations, gender, socioeconomic status (labor and education), prior ED treatments and living situation.

Since BMI can be an important indicator of somatic improvement in EDs, it will be measured repeatedly during the study trial by asking the participants about their height and weight.

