#### Randomization

Random allocation to the control group (continued CBT-E) or the intervention group (GST) will be conducted separately for each treatment location in a ratio of 1:2 by an automatized randomization software program after the completion of the post measurement. This ratio is due to the cluster effect in group-based therapy, which statistically requires more participants for the GST arm than for the continued CBT-E arm. Subsequent to randomization, participants in the GST arm and continued CBT-E arm will complete a baseline measurement (T0). After that, both treatments will start. Post-measurements (T1) will take place on the known end date of the treatment to which a participant is randomized. Follow-up measurements will take place 6 months (T2) and 12 months (T3) later, following initial completion of the entire treatment trajectory at T1. Several clinical measurement instruments are used, see Fig. 1. The current study protocol has been approved by the Medical Research Ethics Committee (MREC) Academic Hospital Maastricht/University Maastricht in The Netherlands, which was formally registered as: NL80491.068.22. The study is registered at ClinicalTrials.gov (registration number NCT05812950), and complies with the World Health Organization Trial Registration Data Set. Modifications to the protocol will be submitted as an amendment and will be examined by the MREC and will be adjusted in the trial registry.

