### Study population

Patients are eligible for participation in the current trial, if they meet the following inclusion criteria: (1) an age of 16 years or older; (2) the ability to read and speak the Dutch language; (3) a DSM-5 classification of anorexia nervosa (AN), bulimia nervosa (BN), or other specified feeding and eating disorder (OSFED) that identifies as an atypical AN or BN variant with a low frequency or limited duration of binges / purges and (4) failure to show an early response after 8 sessions CBT-E. The Jacobson-Truax Reliable Change Index (RCI) approach will be used to assess whether the early CBT-E response is significant or not [35]. Exclusion criteria include: (5) the presence of an acute psychosis; (6) a clinically diagnosed autism spectrum disorder (ASD); (7) currently receiving schema therapy elsewhere and (8) an IQ below 80.

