#### Economic evaluations

Societal costs will be determined using the Treatment Inventory of Costs in Patients with psychiatric disorders questionnaire (TIC-P). This validated instrument assesses costs by measuring consumed healthcare resources and productivity losses [51]. Lastly, the economic evaluation study will be performed in line with the Dutch Guidelines of the National Health Care Institute [52].

During the entire data collection phase, the TIC-P and the aforementioned clinical instruments will be mostly measured on the same time points (T0-T3). See Table 1.

**Table 1 Tab1:** all questionnaires for each measurement point in time

Instruments	Time points^a^					
	Pre-measure	Post-measure	T0	T1	T2	T3
Demographic and clinical characteristics	x					
EDE-Q	x	x		x	x	x
TIC-P			x	x	x	x
EQ-5D-5 L			x	x	x	x
EDQOL			x	x	x	x
SMI-ED			x	x	x	x
YSQ-S3	x			x	x	x
CTQ-SF	x					
BSI			x	x	x	x
CPQ	x					
BMI	x		x	x	x	x

^a^ Pre-measure: measurement before the initial session of CBT-E, post-measure: measurement after 8 sessions of CBT-E, T0: baseline measurement, T1: measurement following the end of treatment, T2: measurement at 6-month follow-up, T3: measurement at 12-month follow-up

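### BMI is built from height and weight that unblinded patients report themselves, so BMI change is change in reported values; fix one height per adult and label BMI as self-reported

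*Protocol article*

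**What the plan says.** The Clinical effectiveness part of the Data collection section describes BMI together with the secondary outcomes. It gives the reason, "Since BMI can be an important indicator of somatic improvement in EDs", and then the method: "it will be measured repeatedly during the study trial by asking the participants about their height and weight". Table 1 schedules BMI at the pre-measure, T0, T1, T2 and T3, but not at the post-measure after eight sessions.

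Three other statements bear on how these values arise.

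- Data collection, on how questionnaires are filled in: "Each measurement will be completed either through hand-based devices (e.g. a smart-phone) or on a computer".
- Data collection, on masking: "blinding of therapists, interviewers, and patients is not possible".
- Randomization: T0 is completed after allocation and before treatment starts.

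The Study population section admits patients from age 16 with anorexia or bulimia nervosa or an atypical variant. The section on the control treatment lists "an excessive evaluation of body image" among the mechanisms thought to maintain the disorder. The article describes no weighing by staff, no measured height and no comparison with clinic records.

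**The concern.** The stated purpose of BMI is to show bodily change, but the stated method yields what patients say about their bodies. In this population, weight is a sensitive quantity. Four of the five scheduled values (T0 to T3) are given after allocation by patients who are not blinded.

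Two kinds of error are at stake. Height restated differently from one occasion to the next makes BMI move when weight has not. If the error in reported weight drifts differently in the two arms, the BMI comparison is biased, and a larger sample does not remove that. A between-arm difference could then reflect reporting, or a true difference could be hidden. What is at stake is any conclusion on somatic improvement, not the primary result.

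**Working it through.** **The plan's own figures.** The article gives no figure for BMI: no expected difference, standard deviation or reporting error. The Sample size section concerns the primary outcome and reproduces: design effect 1 + (8 − 1) × 0.10 = 1.70; 86 × 1.70 = 146.2, stated as 146; 86 + 146 = 232. BMI plays no part in it.

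**Assumptions.** Height 1.65 m and weight 50 kg, with a range of 1.60-1.70 m and 48-55 kg. Misstatements of 1-2 cm and 1-3 kg are illustrations; none comes from the document. BMI = weight / height².

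**Step 1: height restated, weight unchanged.**
- Start: 50 / 1.65² = 18.37.
- Height given as 1.66 m: 50 / 1.66² = 18.14, a false change of −0.22.
- Height given as 1.67 m: 50 / 1.67² = 17.93, a false change of −0.44.
- Over the whole range, 1 cm shifts BMI by 0.19-0.27 kg/m2 and 2 cm by 0.38-0.55 kg/m2.

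**Step 2: one height for all time points, even if it is wrong.** Take a true gain from 50 to 53 kg.
- True height throughout: 3 / 1.65² = 1.10.
- Height wrong by 1 cm but held fixed: 3 / 1.66² = 1.09.
- Height correct first and 1 cm too high later: 53 / 1.66² − 50 / 1.65² = 19.23 − 18.37 = 0.87.

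A fixed height need not be accurate to remove almost all of this error.

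**Step 3: what random height error does to the arm comparison.** If each height answer has an independent error with SD 1 cm, it adds an SD of about √2 × 0.22 = 0.31 kg/m2 to each patient's BMI change. With 86 and 146 patients, this contributes 0.31 × √(1/86 + 1/146) = 0.31 × 0.136 = 0.04 kg/m2 to the standard error of the arm difference. Random height error is therefore mainly noise in individual change.

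**Step 4: weight misstated.** At 1.65 m, an error of 1, 2 or 3 kg shifts a BMI value by 1 / 2.7225 = 0.37, 2 / 2.7225 = 0.73 or 3 / 2.7225 = 1.10 kg/m2. Over 1.60-1.70 m the ranges are 0.35-0.39, 0.69-0.78 and 1.04-1.17.

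**Step 5: which weight error biases the comparison.** Write reported weight as true weight + e. With height fixed, reported change = true change + (e at follow-up − e at T0). A constant e cancels. The bias in the arm comparison is the difference between arms in the mean of (e at follow-up − e at T0), divided by height². A difference of 0.5, 1 or 2 kg gives 0.18, 0.37 or 0.73 kg/m2 at 1.65 m. The document offers no basis for choosing among these values, or zero, or the opposite sign.

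**The case against.** The strongest reply is that the method is openly disclosed, that BMI is not the primary outcome and is not named in the effectiveness hypotheses, and that the figures above are individual shifts under assumed errors. All of this stands and keeps the point modest. Constant misreporting of weight cancels, and random height error hardly moves the arm means (steps 3 and 5). Whether height is asked again at every time point is the natural reading of the text, but it is not spelled out.

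A reader might infer more than the document supports:

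- **That BMI is the only somatic outcome, or the only one that could avoid self-report.** The BSI also rates physical symptoms. Treatment adherence is among the hypotheses, and therapists record attendance. BMI is the only anthropometric measure, and no more than that.
- **That the arms will report weight differently because CBT-E addresses eating and GST addresses schemas.** The contrast is less sharp than this. The GST section ties coping modes to eating disorder symptoms, and both arms receive the same eight CBT-E sessions before randomization. The control-treatment section says nothing about misreporting of weight. Differential reporting is a risk, not a finding.
- **That measured weight should replace self-report at T0 and T1.** With T2 and T3 still self-reported, the planned T1-T2 change would mix two methods. The article also does not say that centres weigh patients.

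What remains is that the article fixes a method that records reported values and presents BMI as an indicator of somatic improvement.

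**Conclusion.** The concern holds in limited form. As planned, BMI change is change in self-reported values from unblinded patients and cannot alone support a claim of somatic improvement. If height is asked anew, each centimetre of difference adds about 0.2 kg/m2 of false individual change at the assumed 50 kg and 1.65 m. Reporting of weight that drifts differently by arm would bias the comparison by about 0.37 kg/m2 per kilogram, but whether this occurs, how strongly and in which direction cannot be determined from the document. The EDE-Q analysis and the sample size are not touched. The change is worth making because its main part is free.

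**What to change.** 1. Use one height per adult participant, taken at the pre-measure, for every BMI. Update height only for participants aged 16-17, who may still grow. This costs nothing.
2. Keep self-reported weight at all scheduled time points as one consistent series, and call BMI self-reported in any conclusion on somatic improvement. This also costs nothing.
3. Where a centre weighs the patient around T0 and T1, record that weight and its date in the patient registration file that therapists already complete after each session. Treat it as supplementary: compare reported with measured weight by arm, and neither replace the self-reported values nor mix the two series.

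The third step adds one extra entry to an existing form. Measured weights will be missing for some patients who stop early and at centres that do not weigh, so the check describes only patients with both values. Therapists are unblinded too, so the check reduces the uncertainty without removing it.

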#### Economic evaluations

Societal costs will be determined using the Treatment Inventory of Costs in Patients with psychiatric disorders questionnaire (TIC-P). This validated instrument assesses costs by measuring consumed healthcare resources and productivity losses [51]. Lastly, the economic evaluation study will be performed in line with the Dutch Guidelines of the National Health Care Institute [52].

During the entire data collection phase, the TIC-P and the aforementioned clinical instruments will be mostly measured on the same time points (T0-T3). See Table 1.

**Table 1 Tab1:** all questionnaires for each measurement point in time

Instruments	Time points^a^					
	Pre-measure	Post-measure	T0	T1	T2	T3
Demographic and clinical characteristics	x					
EDE-Q	x	x		x	x	x
TIC-P			x	x	x	x
EQ-5D-5 L			x	x	x	x
EDQOL			x	x	x	x
SMI-ED			x	x	x	x
YSQ-S3	x			x	x	x
CTQ-SF	x					
BSI			x	x	x	x
CPQ	x					
BMI	x		x	x	x	x

^a^ Pre-measure: measurement before the initial session of CBT-E, post-measure: measurement after 8 sessions of CBT-E, T0: baseline measurement, T1: measurement following the end of treatment, T2: measurement at 6-month follow-up, T3: measurement at 12-month follow-up

#### Process evaluation

In order to measure the extent to which GST is a feasible alternative to CBT-E in clinical practice for patients and therapists, process evaluations will be conducted. More specifically, treatment fidelity (treatment quality), dose delivered (completeness), dose received (exposure and satisfaction), and reach (participation rate) will be assessed in both the GST arm and the continued CBT-E arm.

I.In order to assess dose received, i.e. treatment satisfaction and overall therapeutic alliance, patients will complete a session rating scale (SRS) during each treatment session. The SRS consists of 4 questions regarding key dimensions of effective therapeutic relationships [53].

II. To assess dose delivered and reach, therapists will complete patient registration files after each session. In these files, therapists can describe patient attendance and the extent to which treatment was delivered according to protocol, including potential deviations and additional therapies or medications. These files are expected to assess the true implementation characteristics of the treatment protocol in Dutch clinical practice.

III. Recording of therapy sessions will take place regularly in order to rate overall compliance to the treatment protocol, quality of treatment delivery and the number of patients that were able to participate (fidelity, dose delivered and reach).

IV.After the end of treatment, qualitative interviews will be conducted among certain patients from the GST arm and the continued CBT-E arm, which will take approximately 30 min. Using existing guidelines for qualitative data collection and analysis [54], these interviews are aimed at generating original findings regarding patient experiences that are not identifiable through quantitative approaches. Building upon the SRS, these interviews may identify profound data regarding treatment satisfaction and therapeutic alliance.

